## Sample Size

Considering no study has been performed analyzing the ploidy state, mtDNA content and embryo morphokinetics by PGT-A on IVF/ICSI sibling embryos, we propose a pilot study including 30 couples to assess the feasibility of the study. Moreover, the pilot study will allow us to estimate statistical parameters which enables us to calculate a sample size in a future study in which an acceptable level of power can be established.

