## Subject Inclusion/exclusion criteria

*Inclusion criteria*

- Sperm parameters
  - Sperm concentration before capacitation: >15*10^6^ per ml (WHO)
    - Total motility (PR+NP,%): >40 (WHO)
    - Progressive motility (PR,%):>32 (WHO)
  - Sperm concentration after capacitation: >0.6*10^6^ per ml (not WHO defined)
    - Progressive motility (PR,%):>65 (WHO)
- ≥10 COCs after oocyte retrieval
- BMI ≤30 kg/m^2^
- Female age 18 to ≤ 40 years
- All ovarian stimulation protocols
- Fresh ejaculates
- Presence or absence of sperm morphology data: as we do not have a diagnostic sperm analysis for all patients, the presence or absence of >4% normal morphology (WHO) will not be taken into account, even with known low (<4%) normal morphology
- Couples requesting PGT-A
- Arab population

*Exclusion criteria*

- If after denudation (ICSI) only 2 mature oocytes are obtained
- If all time lapse spaces are occupied
- If the volume to be added after IVF is insufficient to perform IVF on all needed oocytes
- Presence of >1 *10^6^ per ml round cells in the ejaculate
- If a couple’s previous cycle was included in the study

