## Intervention and Follow-up

Couples that are eligible for the study will be selected on the day of OPU based on all inclusion and exclusion criteria (as described under “D. Subject inclusion/exclusion criteria”) and will be asked to participate in the study by signing the IC. A randomization list will determine to which group the first half (or one extra in case an odd number is available) of the oocytes will be assigned. As to prevent selection bias, oocytes will be assigned to both groups under low magnification and different cumulus expansion stages will be evenly divided. Oocytes selected for ICSI will be denuded and injected on the day of OPU after which their pre-implantation development will be followed by time lapse imaging. IVF oocytes will be inseminated (individual or per two) overnight with 10.000 PR sperm cells in a G185 incubator (K systems) and denuded in the morning of day 1 after which they will be transferred to the time lapse imaging incubator. Blastocysts of sufficient quality (to determine this, morphokinetic parameters shall be measured) will be biopsied on day 5-7 after which the blastocysts are vitrified individually. PGT-A (NGS platform) is performed on all TE biopsy samples and the ploidy state and mtDNA score will be provided. All annotated time lapse imaging data will be gathered and combined with the pre-implantation data, PGT-A data (ploidy state and mtDNA copy number) and all general patient and cycle characteristics. Patients with euploid embryos available will receive a FET and implantation rates and (clinical) pregnancy outcomes will be recorded.

The follow-up of the patients does not deviate from a normal fertility trajectory.

Quantification of the determining variables:

The primary outcome variable is the ploidy state

Secondary outcome variables are the (i) embryo development defined by the number of COCs retrieved, maturation and fertilization rate, embryo development analysed on day 3 and day 5, total number of embryos used for the patient, day of biopsy and the morphokinetic parameters; (ii) mtDNA copy number and (iii) the clinical outcome.

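### Feasibility is a stated purpose of the 30-couple pilot, but no outcome measures it, and one exclusion drops couples after oocyte assignment on the ICSI half alone

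*Protocol*

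**What the plan says.** The Sample Size section of the protocol gives two reasons for the number of couples. The first is feasibility: "we propose a pilot study including 30 couples to assess the feasibility of the study". The second is planning: "the pilot study will allow us to estimate statistical parameters which enables us to calculate a sample size in a future study". There is no power or precision calculation, so these two purposes are the whole justification.

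The main aim, the secondary objectives and the Study Variables section list ploidy, pre-implantation development, mtDNA and clinical outcomes. None is a feasibility measure. The nearest statement is the estimate, under Study period and context, that inclusion will take three months.

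The inclusion criteria require "≥10 COCs after oocyte retrieval". Three of the exclusion criteria are practical obstacles to carrying out the split:

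- "If after denudation (ICSI) only 2 mature oocytes are obtained"
- "If the volume to be added after IVF is insufficient to perform IVF on all needed oocytes"
- "If all time lapse spaces are occupied"

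On timing, Intervention and Follow-up says "Couples that are eligible for the study will be selected on the day of OPU based on all inclusion and exclusion criteria". It then describes consent, the randomization list and the assignment of oocytes to the two groups. Only after that does it say "Oocytes selected for ICSI will be denuded and injected on the day of OPU". The IVF half is denuded on the morning of day 1, and no matching exclusion applies to it.

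**The concern.** A pilot that is meant to show whether a split-oocyte design can be carried out needs to count the couples in whom it could not. The mature-oocyte criterion does the opposite. It takes out a couple whose oocytes have already been assigned, because of what was found in one of the two halves.

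Two things are at stake. First, a feasibility statement based on included couples cannot show this failure, so a later study would be planned without knowing how many couples are lost at that step. Second, maturation rate is a secondary outcome compared between the halves. Removing couples with a poor ICSI half, with no equivalent rule for the IVF half, favours ICSI in that comparison.

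**Working it through.** **Plan's own figure.** The 30 couples come from no formula, so there is nothing to reproduce.

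**Order of steps.** Under Intervention and Follow-up the sequence is: eligibility judged on all criteria, consent, assignment from the randomization list, denudation of the ICSI half. The number of mature oocytes after denudation is unknown when eligibility is said to be decided. The two sections therefore do not fit together for this criterion.

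**How often the criterion could apply.** The minimum of 10 complexes gives m = 5 per half. Let p be the probability that an oocyte is mature. The protocol gives no value, so p is an assumption, and oocytes are treated as independent. With X binomial(m, p), P(X ≤ 2) is the chance that the ICSI half has 2 or fewer mature oocytes. P(X = 2) covers the literal reading of exactly 2.

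| m per half | p | P(X ≤ 2) | P(X = 2) |
|---|---|---|---|
| 5 | 70% | 16.3% | 13.2% |
| 5 | 75% | 10.4% | 8.8% |
| 5 | 80% | 5.8% | 5.1% |
| 7 | 70% | 2.9% | 2.5% |
| 7 | 75% | 1.3% | 1.2% |
| 7 | 80% | 0.5% | 0.4% |

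**Effect on ICSI maturation.** Among retained couples the expected ICSI maturity is E[X | X ≥ 3] / m. For m = 5 and p = 75%, P(3) = 0.2637, P(4) = 0.3955 and P(5) = 0.2373, which sum to 0.8965. Then

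(3 × 0.2637 + 4 × 0.3955 + 5 × 0.2373) / 0.8965 = 3.5596 / 0.8965 = 3.971, and 3.971 / 5 = 79.4%.

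This is about 4 percentage points above the assumed 75%. Under independence, the IVF half of the same couples stays at 75%. At m = 7 the same calculation gives about 75.6%, a shift of about 0.6 points.

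**What counting every couple would show.** If a fraction f of attempted couples is stopped, about 30 / (1 − f) must be attempted to include 30. For an assumed f = 10%, 30 / 0.90 = 33.3, so 34 couples: 30/34 = 88% (exact 95% CI 73% to 97%). For f = 20%, 30 / 0.80 = 37.5, so 38 couples: 30/38 = 79% (63% to 90%). Included couples alone would show 30/30 on these stopping reasons in both cases. The values of f are illustrations.

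**The case against.** The strongest reply has four parts.

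1. **Feasibility is wider than completing the split.** A reader might infer that feasibility among the 30 is close to 100% by construction. The protocol does not support that. It defines no feasibility rate, and included couples can still have no normally fertilized zygote, no blastocyst to biopsy or no PGT-A result in one half. Inclusion can also overrun three months. For example, if 20% to 50% of assigned oocytes give a biopsiable blastocyst (assumed, independent oocytes) with 5 or 7 per half, the share of couples with at least one in both halves runs from about 45% to 98%. This part stands. Only the excluded failure modes are hidden.

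2. **Not all three criteria are failures of the split.** Time-lapse occupancy can be known before any oocyte is assigned, and the timing of the volume criterion is unclear from its wording. This also stands. Only the mature-oocyte rule clearly comes after assignment.

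3. **Replacement and the size of the harm.** A reader might infer that dropped couples are replaced, or that later recruitment would be understated by some 10% to 33%. The protocol is silent on replacement, and those percentages follow from assumed failure counts (3 of 33 and 10 of 40), not from the document. If the later study kept the same criteria, ploidy estimates from included couples would still be the relevant input for the number to include. The excluded couples bear on how many must be approached.

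4. **Feasibility measures and participant flow belong in an SAP or the report.** In general this is fair, and the SAP is not shown. It does not answer the point here. The purpose and the post-assignment exclusion are both protocol text, and they work against each other. Whether dropped couples are logged has to be settled before inclusion starts.

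**Conclusion.** The point holds in a limited form. Feasibility is a stated purpose without an outcome or denominator. At least one exclusion is applied after consent and oocyte assignment, on the ICSI half only. Restricting results to included couples hides that failure and raises ICSI maturation relative to IVF.

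The effect is material near the 10-complex minimum: about 6% to 16% of couples for assumed maturity of 80% to 70%, with ICSI maturity rising from an assumed 75% to about 79%. At 7 per half and the same 75%, about 1% of couples are affected. These figures assume independent oocytes, and they read the criterion as 2 or fewer mature oocytes. The actual distribution of cohort sizes is not given. Ploidy estimation, the pilot's other purpose, is not made trivial by this, although its estimates would apply to the selected couples.

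This should be changed before inclusion starts. It does not invalidate the design.

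**What to change.** In the Sample Size section, define the feasibility outcomes:

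- **(a)** Among all couples with at least 10 complexes who are otherwise eligible on the day of retrieval, whether or not they consented: the number and percentage (exact 95% CI) stopped for each of the three reasons, separated into before and after oocyte assignment. A denominator of consenting couples would miss those turned away before consent, for example for lack of a time-lapse place.
- **(b)** Among all couples whose oocytes were assigned: the percentage with at least one blastocyst with a ploidy result in both halves.

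Keep couples dropped after assignment in the participant flow, in these denominators and in the maturation-rate analysis. State whether they count toward the 30. Say whether the mature-oocyte criterion means exactly 2 or at most 2, and reconcile the exclusion criteria with Intervention and Follow-up on when eligibility is decided.

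The cost is a screening log, one table and a slightly less favourable feasibility figure. No treatment step changes.

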# Abstract

ICSI is commonly used in PGT cases to eliminate any risk of sperm DNA contamination. With the switch from cleavage stage biopsy to biopsy of the full (hatching) blastocyst, this potential risk of contamination can be neglected and could allow the use of conventional IVF in PGT cases. Especially in cases of non-male factor infertility, the use of conventional IVF can be applied as a more ‘natural’ insemination method.

A pilot study will be performed on sibling oocytes including patients with non-male factor infertility and requesting PGT-A (NGS platform). If at least 10 cumulus oocyte complexes (COCs) are obtained after oocyte retrieval, half of the oocytes will be subjected to ICSI and the other half to conventional IVF. Preimplantation development is followed by time lapse imaging and blastocysts (day 5-7) fulfilling the biopsy criteria will undergo trophectoderm biopsy to detect the ploidy state and the mtDNA copy number.

The main objective is to analyse if the use a more physiological insemination method (IVF) has a beneficial impact on the ploidy state of the blastocyst as compared to ICSI within the same patient. As the embryos will be cultured in a time lapse imaging system, annotations can be made and the differences in maturation rate, fertilization rate and embryo development between both insemination methods can be analysed as secondary outcome parameter. On top of this, the PGT-A outcome will also display the mtDNA copy number which can be compared between IVF and ICSI biopsied sibling blastocyst. Euploid blastocysts will be transferred in subsequent FET cycles and give an indication on the clinical outcome between IVF and ICSI.

Would this study enable us to undermine the dogma to perform ICSI for all PGT cycles?

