## Study Variables

### Main-outcome measures (Dependent)

PGT-A:

- Ploidy outcome: euploid or aneuploid

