### Objectives assessment

Main objective

In order to compare the effect of IVF versus ICSI on the blastocyst ploidy state a Poisson regression will be performed, which is the most appropriate statistical modelling method to analyse count data.

Secondary objectives

To compare IVF versus ICSI outcomes in preimplantation development outcomes:

- To compare the maturation rate, a t-test will be used to detect differences in the average number of mature oocytes (a Wilcoxon test will be used if we cannot assume normal distribution of data). If we found differences, linear or Poisson regressions will be performed to evaluate them in a model taking into account rest of explanatory variables.
- To compare the fertilization rate, a t-test will be used to detect differences in the average number of zygotes with 2PN oocytes (a Wilcoxon test will be used if we cannot assume normal distribution of data). If we found differences, linear or Poisson regression will be performed to evaluate them in a model taking into account rest of explanatory variables.
- In order to compare embryo quality on D3 (measured using the Istanbul consensus), a multinomial logistic regression will be performed.
- Embryo quality D5
  - To compare the blastulation rate, a t-test will be used to detect differences in the average number of embryos reaching at least the BL1 stage (a Wilcoxon test will be used if we cannot assume normal distribution of data). If we found differences, linear or Poisson regressions will be performed to evaluate them in a model taking into account rest of explanatory variables.
  - In order to compare embryo quality on D5 (The expansion stage of the blastocyst and the quality of the ICM and TE will divide the embryos into 3 categories), a multinomial logistic regression will be performed.
- To compare the utilization rate, a t-test will be used to detect differences in the number of embryos that can be used for the patient (a Wilcoxon test will be used if we cannot assume normal distribution of data). If we found differences, linear or Poisson regressions will be performed to evaluate them in a model taking into account rest of explanatory variables.

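### The pilot is meant to supply the parameters for a future sibling-oocyte study, but its fixed analyses carry no couple effect and so omit the within-couple ones

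*Protocol*

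**What the plan says.** The protocol gives 30 couples two purposes (Sample Size). The first is feasibility: "we propose a pilot study including 30 couples to assess the feasibility of the study". The second is to prepare a larger study: "the pilot study will allow us to estimate statistical parameters which enables us to calculate a sample size in a future study". Power is left to that later study, which is described as one "in which an acceptable level of power can be established". The section does not name the parameters.

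The design is within couple. According to the Abstract, "half of the oocytes will be subjected to ICSI and the other half to conventional IVF", and the effect of IVF is to be judged "as compared to ICSI within the same patient". Entry requires "≥10 COCs after oocyte retrieval", so each method receives at least about five complexes. The primary outcome is binary for each biopsied blastocyst: "Ploidy outcome: euploid or aneuploid".

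The analyses are fixed under Statistical data analysis:

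- **Exploratory data analysis:** frequency tables for categorical data; mean, standard deviation and confidence interval for continuous data.
- **Homogeneity analysis:** chi-square, Student t or Mann-Whitney tests between the study groups.
- **Objectives assessment, main objective:** for ploidy, "a Poisson regression will be performed, which is the most appropriate statistical modelling method to analyse count data". No couple term is mentioned.
- **Objectives assessment, secondary objectives:** t or Wilcoxon tests, chi-square tests, and linear, Poisson, logistic or multinomial regressions, plus growth models fitted per embryo. None is said to be paired or to carry a couple effect.

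The list of explanatory variables contains the insemination method and patient and cycle characteristics, but no couple identifier.

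**The concern.** In a sibling-oocyte design the couple is its own control. Blastocysts from one couple share parents and one retrieval, so their ploidy results may be correlated. The precision of the IVF-ICSI comparison depends on that correlation and on how many couples contribute a biopsied blastocyst to both arms. Anyone sizing a later study of this design needs both quantities.

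The protocol promises parameters for that calculation, yet the analyses it fixes read as if the two arms were independent groups. Mann-Whitney is by definition a test for independent groups. If the plan is followed to the letter, the pilot reports how often blastocysts are euploid and how many there are, but not how strongly siblings resemble each other. The later study would then rest on a guess for the feature that distinguishes this design from a parallel-group one.

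**Working it through.** **1. The plan's own figure.** The 30 couples cannot be reproduced, because no alpha, power, effect, euploidy rate, blastocyst yield or precision target is attached to them. The number is a chosen pilot size. Every other input below is an assumption and is labelled so.

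**2. What a future sibling study needs, and what the planned analyses return.**

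| Parameter | Returned as written? | Where |
|---|---|---|
| Euploid proportion | Yes | Frequency tables of the ploidy outcome |
| Biopsied blastocysts per couple per arm | Largely | Utilization rate and the biopsy yes/no variable |
| Share of couples with a biopsied blastocyst in both arms | No | No analysis named |
| Within-couple correlation, or SD of the within-couple difference | No | No couple effect or stated pairing |

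**3. Effect of leaving out the correlation.** Let p be the euploid proportion, m the biopsied blastocysts per couple per arm (equal in both arms) and ρ the correlation between any two siblings. For one couple, the variance of the difference in proportions is

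2p(1−p)/m × [1 + (m−1)ρ − mρ] = 2p(1−p)(1−ρ)/m.

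A calculation from marginal rates alone omits the factor (1−ρ) and overstates the required size by 1/(1−ρ):

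- ρ = 0.1: 1/0.9 = 1.11-fold too large
- ρ = 0.2: 1/0.8 = 1.25-fold too large

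Two qualifications apply. First, the factor assumes equal numbers per arm within each couple. In a simulation with independent Poisson counts per arm, the crude pooled difference gained nothing from the correlation: with a mean of 3 per arm the half-width was 14.7, 14.6 and 14.7 points at ρ = 0, 0.1 and 0.2. Second, if the IVF-ICSI effect itself varies between couples with SD τ, the error runs the other way. With τ = 0.2, m = 3, p = 0.5 and ρ = 0, the variance is multiplied by 1 + τ²m/[2p(1−p)] = 1 + 0.04×3/0.5 = 1.24. Marginal rates cannot show which case applies.

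**4. Share of couples with both arms.** Assume independent Poisson counts with mean m per arm. The expected number of couples with at least one blastocyst in each arm is 30 × (1 − e^−m)².

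- m = 1.5: 30 × 0.777² = 18.1 couples
- m = 3: 30 × 0.950² = 27.1 couples

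This share can therefore be well below one and is worth reporting.

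**5. Precision of the arm difference (caution only).** The 95% half-width is 1.96 × √[2p(1−p)(1−ρ)/(30m)], with p = 0.5.

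- m = 1.5, ρ = 0: 1.96 × √(0.5/45) = 20.7 points
- m = 4, ρ = 0.2: 1.96 × √(0.4/120) = 11.3 points

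The lower figure also supposes equal arms within couples and an analysis that uses the pairing. With ρ = 0 and m = 4 it is 12.7.

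**6. Precision of the correlation.** For 30 couples with five blastocysts each and ρ = 0.10, the standard error is (1−ρ)(1+4ρ)√[2/(5×4×29)] = 0.9 × 1.4 × 0.0587 = 0.074. The interval runs from about 0 (truncated) to 0.10 + 1.96 × 0.074 ≈ 0.25. That is wide, but it bounds the value.

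**The case against.** The strongest reply is that nothing is lost. Couple-level data will be collected, so the correlation and the share of informative couples can be computed at any time. The t-test and Wilcoxon test could be run in paired form, and a statistical analysis plan that is not at hand may add a couple term. Two of the four parameters already follow from the planned summaries. A pilot need not be powered, and the protocol defers power openly.

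Much of this stands. Thirty couples is not an error, wide intervals are normal in a pilot, and the omission is recoverable. It does not remove the mismatch: the protocol itself states the purpose and itself fixes the analyses, and the second does not fully serve the first.

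A reader might also infer that the future study will come out several-fold too small. The documents do not support that. It would require the pilot's observed difference to be adopted as the design effect, which Sample Size never says. On that condition, with a true 10-point difference, 50% euploidy and 1.5 to 5 blastocysts per arm, the chance of being more than two-fold too small is 36% down to 24%. If instead the difference is chosen beforehand and only the couple-level variance comes from 30 couples, the ratio of true to estimated variance has a 95% range of 0.63 to 1.81 (chi-square, 29 degrees of freedom). Nor does the missing correlation lead to a study that is too small: ignoring a positive correlation by itself makes it too large. Finally, the protocol has no go/no-go rule, so nothing suggests that a chance reversal would end the programme.

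**Conclusion.** The point holds in a limited form. The protocol says the pilot will provide the parameters to size a future study, but the fixed analyses, followed as written, omit two that a sibling design needs: the within-couple correlation (or the SD of the within-couple difference) and the share of couples with a biopsied blastocyst in both arms. The purpose is partly delivered.

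The consequence is moderate: about 1.25-fold too large at an assumed correlation of 0.2 with balanced arms, less if the arms are unbalanced, and possibly in the opposite direction if the effect differs between couples. The ±11 to ±21 points are a caution about using the observed difference, not a fault in the sample size. They rest on assumed yield, euploidy and correlation; only the 30 couples come from the protocol.

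**What to change.** **Objectives assessment, main objective.** Analyse ploidy per biopsied blastocyst with a model that carries a couple effect, for example a logistic model with a random couple intercept, so that the comparison is made within couples and the correlation is estimated.

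**Sample Size.** List the outputs to be carried forward, each with a 95% confidence interval: euploid proportion; biopsied blastocysts per couple per arm; share of couples with at least one in both arms; within-couple correlation. Add one sentence noting that the arm difference from 30 couples will be imprecise and should not by itself set the effect size of the future study.

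**Cost.** A few sentences and a little extra analysis of data already planned for collection. The couple-level intervals will be wide and must be reported as such. No change to the number of couples or to procedures is needed.
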